### Study protocol

The study period will be brief to reduce the likelihood that changes in outcomes are due to dementia progression, inter-current illness or other incidental events. Activity sessions must be long enough to detect changes in selected outcomes during the carer's visit, but not so long that sessions are likely to be interrupted by meals or nursing interventions. In our recently completed Montessori study [25], the choice of 30-minute sessions has worked well. A study period of up to four weeks has also proved feasible. We will therefore employ an exposure of six sessions spread over a three week period for both conditions. The choice of condition (treatment or control) will be randomly determined using Excel. The program from week 1 (W1) to week 5 (W5) is shown in Table 1. Baseline measures will be conducted at the start of the Montessori workshop or dementia education session (W1). All participants will receive a follow-up phone call half way through W2-W4 to ascertain they have filled out questionnaires after each visit. A face-to-face appointment will be made to complete the final measurements at the end of W4.

**Table 1 T1:** Program for treatment and control condition groups

	Treatment group	Control group
W1	Group Montessori workshop	Dementia education session

	↓	↓

W2 W3 W4	6 Montessori sessions	Waiting list period

		↓

W5		Group Montessori workshop

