##### Other measures

Measures collected at baseline will include residents' and carers' socio-demographic details, type of relationship (friends and neighbours can be included if they meet criteria), duration of caring, the frequency and length of visits, and quality of the pre-morbid relationship. We will abstract the date of admission to the facility from the resident's file and will complete the Clinical Dementia Rating Scale (CDR) [32] and Cohen Mansfield Agitation Inventory [33] with a staff member to establish dementia severity and level of agitation.

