### Sample size calculation

The sample size calculation is based on a study comparing wives caring for moderately impaired husbands that exhibit probable Alzheimer's disease with wives whose spouses demonstrate no mental or physical condition matched on sociodemographic background [34]. We calculated means per group (carers vs. non-carers) for the total Mutuality Scale of the Family Caregiving Inventory [28]. Caregiving wives reported a score of 2.89 and the control participants a score of 3.48 (pooled SD = 0.74), with higher scores indicating a higher quality of the relationship (effect size 0.80). We have used G*Power 3.1.2 (test family = t-test, statistical test = means: difference between two independent means (two groups), alpha = 0.05, power = 0.80 and effect size *d *= 0.80) to calculate that 21 participants in each condition would suffice to reveal such a difference. We estimate 20% attrition and will recruit 50 carers.

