### Statistical analysis

We will use independent t-tests to compare the means of outcome measures for the Montessori and control conditions. Next, each outcome measure will be subjected to a 2-way ANOVA with condition (Montessori *vs*. control) as fixed factor. We will then undertake ANCOVAs to investigate whether the intervention enhances certain outcomes (e.g. quality of relationships) after controlling for others (e.g. quality of pre-morbid relationships) to explore the possibility of mediation. Secondly, we will extend these models to examine whether other factors, such as resident-carer relationship (e.g. spouse *vs*. child) and dementia severity (moderate *vs*. severe) serve to moderate treatment benefits. Finally, we will conduct a multilevel variant of these ANOVAs to include higher level factors such as the aged care facility.

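### The mediation ANCOVA is exemplified by pre-morbid relationship quality, a baseline covariate that the intervention cannot change, so that adjustment cannot show mediation

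*Protocol article*

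**What the plan says.** In the protocol article, the Statistical analysis section sets out t-tests, then ANOVAs, then ANCOVAs. The ANCOVAs are to examine "whether the intervention enhances certain outcomes (e.g. quality of relationships") "after controlling for others (e.g. quality of pre-morbid relationships) to explore the possibility of mediation". No other variable is named for this step.

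The Other measures section lists the same variable among the baseline data. The list opens with "Measures collected at baseline will include residents' and carers' socio-demographic details" and ends with "the frequency and length of visits, and quality of the pre-morbid relationship". It is not among the primary or secondary outcomes.

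The Study protocol section fixes the timing: "Baseline measures will be conducted at the start of the Montessori workshop or dementia education session (W1"). The Experimental conditions section gives the first half hour of each session to the baseline questionnaires, ahead of the teaching.

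Moderation is planned as a separate step. The sentence after the ANCOVAs asks whether carer-resident relationship and "dementia severity (moderate *vs*. severe) serve to moderate treatment benefits".

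**The concern.** A mediator lies on the path from allocation to outcome: the intervention changes it, and it in turn changes the outcome. How close two people were before the illness cannot be altered by a workshop held years later or by six visits after it. It can predict the outcome, and it can mark carers who benefit more or less, but it cannot carry the effect.

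The stated purpose and the named variable therefore do not fit. Two things are at stake. If the intervention works through some other route, this ANCOVA will not reveal it. If the arms differ by chance in pre-morbid quality, the condition effect will move on adjustment, and under the stated purpose that movement could be read as a sign of mediation. How the intervention works is a planned question, and the analysis as exemplified cannot answer it.

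**Working it through.** The plan gives no figure for this point, so there is none to reproduce. The check has a logical part and two illustrations. The only planned numbers used are 50 carers recruited and 2 × 21 = 42 carers analysed (Sample size calculation). Every effect size below is an assumption.

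**1. The path.** In a simple mediation model, indirect effect = a × b, where a is the effect of condition on the mediator and b is the effect of the mediator on the outcome.
- Pre-morbid quality is fixed before the intervention, so a = 0.
- The indirect effect is 0 × b = 0, whatever the value of b.

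**2. What adjustment does to the condition effect.** Assumed model: condition to true mediator 0.8, true mediator to outcome 0.8, baseline covariate (SD 1) to outcome 0.5, mediator residual SD 1, outcome residual SD 0.6. Carers are allocated individually with no clustering, and there are 20,000 simulated trials at each size. The true total effect is 0.8 × 0.8 = 0.64, all of it mediated.

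| Adjustment | Mean change in condition effect, N = 50 | N = 42 | Effect after adjustment |
|---|---|---|---|
| Baseline covariate | −0.001 (SD 0.15) | −0.001 (SD 0.16) | 0.64 |
| True post-allocation mediator | 0.640 (SD 0.25) | 0.640 (SD 0.27) | 0.00 |

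Change means unadjusted minus adjusted. Adjusting for the baseline covariate leaves the effect at 0.64 on average, although the effect is fully mediated by something else.

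The spread in the first row is chance imbalance. A hand check: the shift is about 0.5 × (difference in covariate means), and with 25 per arm that difference has SD √(2/25) = 0.283. This gives 0.5 × 0.283 = 0.14, close to the simulated 0.15. A single trial can thus show a visible shift in either direction with no mediation through that variable.

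**3. If another trial outcome is controlled for instead.** A smaller condition effect is then not proof of mediation either, because two carer self-reports may share causes. Assumed model: M = 0.5T + 0.6U + e and Y = 0.3T + 0.6U + e, with T the condition, U an unmeasured shared cause with SD 1, and the residuals e independent with SD s. M has no effect on Y. The condition effect adjusted for M is 0.30 − 0.5 × 0.36 / (0.36 + s²).
- s = 0.8: 0.30 − 0.5 × 0.36/1.00 = 0.12, a shrinkage of 0.18/0.30 = 60%.
- s = 1.0: 0.30 − 0.5 × 0.36/1.36 = 0.168, a shrinkage of 0.132/0.30 = 44%.

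The range of 44% to 60% belongs to these assumed paths and is not an estimate for this trial. It shows only why the caveat in the fix is needed.

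**The case against.** The strongest defence has four parts.

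- **The example is only an example.** The wording allows other outcomes and other control variables, and an ANCOVA on visit mastery could explore mediation. This stands, and it limits the point. A reader might infer that the whole mediation plan is incapable of showing mediation, but the text does not support that. It does not clear the passage, because the one variable named cannot serve and no suitable one is named.
- **No decision rule is set.** A reader might infer that any drop in the condition coefficient will be reported as mediation. The protocol says only that the possibility will be explored, and gives neither a threshold nor a reporting commitment. The risk of misreading follows from the stated purpose and is not a stated intention.
- **Mediation may be a slip for moderation.** Moderation has its own sentence directly afterwards, with other factors. It also needs an interaction term, which controlling for a variable does not supply.
- **The detail may be in a fuller document.** The choice of mediator and the method for an indirect effect can fairly be left there, and their absence is no fault. The point is narrower: a named covariate is given a purpose that it cannot serve.

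It also stands that adjusting for pre-morbid quality is sound in itself. Only the interpretation attached to it is wrong.

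**Conclusion.** The point holds in limited form. As exemplified, the ANCOVA adjusts for a baseline covariate and cannot bear on mediation. The expected change in the condition effect is zero, and any change seen in about 50 carers reflects chance imbalance, with SD about 0.15 under the assumed values.

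The zero expectation assumes that the carer's rating of the pre-morbid relationship does not depend on the condition. The rating precedes the training content, which supports this. The figure of 0.15 also assumes individual allocation. The trial allocates facilities, and the documents give no figure for how far this rating clusters by facility.

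Severity is minor. The step is exploratory, and the main comparison between conditions does not depend on it.

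**What to change.** Describe pre-morbid relationship quality as a baseline covariate, or as a moderator tested with a condition interaction, and remove the mediation interpretation from that adjustment.

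If mediation is intended, name a measure taken after allocation that is already collected in both arms. Mean visit satisfaction or mean visit mastery over W2 to W4 would do, with the end-of-W4 relationship, mood or quality-of-life scores as outcomes. Adjust for the baseline value of the outcome. For visit mastery, also adjust for the baseline global mastery score, which uses matching items. No baseline visit rating is described, so visit satisfaction has no direct baseline counterpart.

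Report the result as exploratory, and state that carer self-reports may share causes, so a smaller condition effect after adjustment is not by itself proof of mediation.

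The cost is a change of wording and a little analysis work. No new data are needed and the sample size does not change.

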## Discussion

Montessori activities and other one-to-one interactions have successfully reduced agitation and increased positive affect and engagement in people with dementia. Helping family carers to deliver these activities in a residential setting is likely to make visits more satisfying and improve the quality of life for both the carers and the care-recipients. These beneficial effects might also reduce nursing staff burden and thus impact positively on residential facilities.
